## Abstract

**Background:**

Increased levels of cortisol during acute alcohol withdrawal have been linked to cognitive deficits and depression. Preclinical research found that the glucocorticoid Type II receptor antagonist, mifepristone, prevented some of the neurotoxic effects of withdrawal and memory loss. Clinical trials have shown mifepristone effective in the treatment of depression. This study aims to examine the extent to which the glucocorticoid Type II receptor antagonist, mifepristone, when given to alcohol dependent males during the acute phase of alcohol withdrawal, will protect against the subsequent memory loss and depressive symptoms during abstinence from alcohol.

**Methods/Design:**

The study is a Phase 4 therapeutic use, “Proof of Concept” trial. The trial is a double-blind randomised controlled clinical trial of mifepristone versus inactive placebo. The trial aims to recruit 120 participants referred for an inpatient alcohol detoxification from community alcohol teams, who meet the inclusion criteria; 1) Male, 2) Aged 18–60 inclusive, 3) alcohol dependent for 5 or more years. A screening appointment will take place prior to admission to inpatient alcohol treatment units to ensure that the individual is suitable for inclusion in the trial in accordance with the inclusion and exclusion criteria. On admission participants are randomised to receive 600 mg a day of mifepristone (200 mg morning, afternoon and evening) for 7 days and 400 mg for the subsequent 7 days (200 mg morning and evening) or the equivalent number of placebo tablets for 14 days. Participants will remain in the trial for 4 weeks (at least 2 weeks as an inpatient) and will be followed up at 3, 6 and 12 months post randomisation. Primary outcome measures are cognitive function at week 3 and 4 after cessation of drinking and symptoms of depression over the 4 weeks after cession of drinking, measured using the Cambridge Neuropsychological Test Automated battery and Beck Depression Inventory, respectively. Secondary outcome measures are severity of the acute phase of alcohol withdrawal, alcohol craving, symptoms of protracted withdrawal and maintenance of abstinence and levels of relapse drinking at follow-up.

**Discussion:**

The current trial will provide evidence concerning the role of glucocorticoid Type II receptor activation in cognitive function and depression during acute alcohol withdrawal and the efficacy of treatment with mifepristone.

**Trial registration:**

ISRCTN: ISRCTN54001953, Registered 29th September 2011.

## Background

Cognitive deficits are seen in 50 to 80 % of those dependent on alcohol [1] currently there is no effective treatment. The cognitive functions particularly affected in alcohol dependence are learning new skills, visuospatial ability, executive function (planning, capacity for abstraction and effortful processing), and aspects of attention, whilst verbal skills usually remain intact [2–6]. The cognitive deficits not only affect the quality of life of those dependent on alcohol and the amount of health care they need, but also have a detrimental effect on ability to benefit from treatment programmes [4, 7, 8]. Depression is a major symptom in many people who are dependent on alcohol, and is associated with greater tendency to relapse drinking [9]. Most depressive symptoms in this population are secondary to the alcohol dependence and gradually resolve spontaneously. Despite this, improvement in symptomatology could provide faster and more complete recovery and would aid abstinence.

The majority of those dependent on alcohol undergo frequent episodes of withdrawal and resumption of drinking, and clinical evidence indicates that “kindling” occurs, as a higher number of withdrawal episodes are associated with greater severity of withdrawal, including greater memory impairment [10]. Schandler et al. [11] found visuospatial learning was worse in those dependent on alcohol during abstinence than in those who were still intoxicated. People who experienced more alcohol withdrawal episodes have been found to have greater subsequent memory deficits [12]. Preclinical data also demonstrated that withdrawal is an important factor in causing the memory deficits. Memory and learning deficits were found in rats in a variety of tests after alcohol withdrawal, but not during alcohol intake [13, 14]. These data suggest that the neurotoxicity that is known to occur during acute alcohol withdrawal may play a contributory role in the subsequent cognitive deficits so frequent in those who are dependent on alcohol [15].

Benzodiazepine drugs are normally prescribed during alcohol detoxification to reduce the overt symptoms of alcohol withdrawal (tremor, and potentially fatal convulsions) but these drugs do not prevent the longer term consequences of cognitive deficits, depression, alcohol craving and relapse back into alcohol drinking [4, 12, 16]. However, drugs that act at different target sites from that of the benzodiazepines could have prolonged beneficial effects. The acute alcohol withdrawal phase therefore offers a potential therapeutic window for intervention that has previously been little explored.

There is a high level of release of glucocorticoids (cortisol in humans, corticosterone in rodents) from the adrenals during the acute alcohol withdrawal period. High glucocorticoid levels are well established to cause memory loss in both humans and animals [17]. High circulating concentrations of cortisol and corticosterone activate the Type II glucocorticoid receptor. These hormones increase the neurotoxic effects of *N*-Methyl-D-aspartate (NMDA) and other excitatory amino acids [18]. An important link between cortisol and memory loss was found by Errico et al. [19] who showed the severity of cognitive deficits in alcohol-dependent persons was correlated not only with a greater number of withdrawal episodes but also with higher cortisol levels during acute withdrawal. There is also evidence relating depressive symptoms and cognitive deficits [20]. Although the direction of any potential cause/effect relationship is not yet fully understood, glucocorticoids have been implicated in both problems [21].

Mifepristone is an antagonist at the Type II glucocorticoid receptor. Administration of mifepristone to mice during the acute phase of alcohol withdrawal was found to reduce the subsequent memory loss [22]. Parallel studies, using an organotypic culture model of alcohol withdrawal, showed that high glucocorticoid concentrations of glucocorticoid increased the neurotoxic consequences of alcohol withdrawal. Application of the Type II glucocorticoid receptor antagonist, mifepristone, prevented this neurotoxicity [23]. In preclinical studies, mifepristone also reduced the behavioural signs of acute alcohol withdrawal [23, 24]. Voluntary alcohol consumption in rodents, and increases in this caused by mild stress, were reduced by administration of mifepristone [25, 26]. Fahlke and colleagues [27, 28] showed that administration of corticosterone increased voluntary alcohol drinking in rats, while reduction in glucocorticoid synthesis, or adrenalectomy, decreased alcohol intake. Importantly for the current study, Vendroluscolo et al. [29] showed that mifepristone reduced the increase in operant responding for alcohol seen in alcohol-dependent rats, without affecting responding in rats not dependent on alcohol. In a recent clinical trial, mifepristone was administered at 600 mg daily for 1 week to alcohol-dependent individuals who continued to drink alcohol for the first 4 days of the treatment. Reductions in alcohol-cue craving and in self-reported alcohol consumption were seen after 1 week of treatment, and in the latter at 1 week post treatment [30].

Clinical studies have found mifepristone also has a beneficial effect in depression [31–35] with a more rapid action than conventional antidepressants [34]. A clinical pilot study found mifepristone alleviated both the cognitive deficits and the depressive symptoms in bipolar depression [35]. However, a subsequent larger study by the same research group found only cognitive deficits were alleviated, specifically spatial working memory [36]. There are no published reports of glucocorticoid antagonist trials for treatment of depression in alcohol-dependent individuals, although in some alcoholics, conventional antidepressant drugs both alleviated depressive symptoms and decreased relapse drinking [37].

### Aims of the study

The current study aims to examine the extent to which the Type II glucocorticoid receptor antagonist, mifepristone, when given to alcohol-dependent persons during the acute phase of alcohol withdrawal, will protect against the subsequent memory loss and depressive symptoms during abstinence from alcohol. The results will provide information about the extent of the contribution of glucocorticoids to these problems, which will aid future development of treatment for alcohol dependence.

### Objectives

To compare effects of mifepristone and placebo in preventing memory loss and depressive symptomatology in alcohol-dependent persons undergoing alcohol detoxification, using the Cambridge Neuropsychological Test Automated battery (CANTAB) and Beck Depression Inventory (BDI-II) [38], respectively.To compare effects of mifepristone and placebo on the severity of the acute phase of alcohol withdrawal, alcohol craving and the symptoms of protracted withdrawal.To compare effectiveness of mifepristone and placebo in maintaining abstinence from alcohol and levels of relapse drinking at 3, 6 and 12 months follow-up from cessation of alcohol consumption.

## Methods/Design

The design of the current study is a double-blind randomised controlled clinical trial of mifepristone and inactive placebo. The study is a Phase 4 therapeutic use, “Proof of Concept” trial. Ethical approval has been granted by the London–Dulwich Research Ethics Committee (reference: 10/H0808/7) and complies with UK and European Good Clinical Practice for medicinal trials guidelines. Participants will be recruited from Community Alcohol Teams serving 5 inpatient alcohol treatment units in 3 regions of England (South London, Sussex, Kent, Hull and Barnsley). Participants will be given mifepristone/placebo for 2 weeks while they are in patients undergoing detoxification from alcohol. They will then remain in the trial for a further 2 weeks undergoing cognitive testing and questionnaires, with follow-up contact at 3, 6 and 12 months subsequent to alcohol cessation.

### Hypotheses

Treatment with mifepristone will result in improved memory and/or depressive symptomatology outcomes compared with placebo.Relapse drinking rates will be reduced in those treated with mifepristone compared with placebo.Activation of Type II glucocorticoid receptors during the acute phase of alcohol withdrawal is causally involved in the subsequent cognitive deficits, symptoms of depression and/or relapse drinking following acute cessation of alcohol consumption.

### Inclusion criteria

Diagnosis of alcohol dependence by DSM-IV for 5 years or moreMaleAged between 18 and 60 years (inclusive)Willingness to provide informed consent.

### Exclusion criteria

Clinical diagnosis of a neuroendocrine disorderLiver damage, determined at screening by alanine aminotransferase (ALT) activity of more than 2.5 times the normal rangeRenal dysfunction, as determined by creatinine levels over 150 μmol/L in plasma samples taken prior to admission to the Alcohol UnitDocumented evidence of a psychotic disorderSevere brain damage or severe mental impairmentDiagnosis of severe physical illness that would preclude participation (e.g. terminal illness),Documented evidence of current dependence on a substance other than alcohol or nicotine.Inability to understand sufficient English to understand the information needed for the cognitive testingWernicke-Korsakoff syndromes Porphyria Severe asthma uncontrolled by therapy Cardiac disorders i.e. myocardial infarction, congestive cardiac failure or cardiomyopathy Persistent high blood pressure (over 160 mmHg systolic and/or 100 mmHg diastolic on both of two readings at initial screening session Medical history of diabetes A known allergy to mifepristone Owing to potential interactions with mifepristone, participants taking the following drugs will be excluded unless a suitable alternative can be prescribed: ketoconazole, itraconazole, metronodazole, miconazole, erythromycin, clarithromycin, rifampin, rifabutin, norfloxacin, nelfinavir, ritonavir, saquinavir, zafirlukast, fluvoxamine, quinine, phenytoin, phenobarbital, primadone, carbamazepine, amiodarone, warfarin, corticosteroids or St John’s Wort. Consumption of grapefruit juice is also contraindicated during the mifepristone treatment.

### Study entry

Prospective participants who are referred for an admission to an alcohol inpatient unit for alcohol detoxification will be identified by the community alcohol teams. If the person is willing to hear more about the research, contact details will be passed to the research team. Written informed consent to complete a preliminary screening appointment will be taken. Eligibility to take part in the research will be checked at a preliminary screening appointment and included administration of the Mini-Mental Sate Examination (MMSE) [39] to screen for any severe cognitive impairment. The Composite International Diagnostic Interview (CIDI) [40] will be administered to demonstrate alcohol dependence of at least 5 years of the patients prior to detoxification according to DSM-IV diagnostic criteria. Plasma alanine aminotransferase (ALT) and creatinine will be measured for indication of liver damage and impaired renal function, respectively. Urine will be tested for evidence of porphyria. If the participant is eligible, consent to take part in the study will be obtained prior to or on admission to the alcohol unit by a clinical member of the research team or a delegated physician. All participants will be advised not to consume grapefruit juice during the trial as this is contraindicated with mifepristone.

At the preliminary screening appointment participants will be asked to complete questionnaires to help establish patterns of alcohol consumption. This includes a measure of the severity of alcohol dependence using the Severity of Alcohol Dependence Questionnaire (SADQ) [41], current craving for alcohol using the Alcohol Urge Questionnaire (AUQ) [42], problems experienced due to alcohol using the Alcohol Problems Questionnaire (APQ) [43], and a retrospective report of the quantity of alcohol consume over the previous 90 days collected using the time-line follow-back (TLFB) [44]. In addition, the Fagerstrom questionnaire [45] will be used to record the amount of smoking and level of nicotine dependence and symptoms of depression will be measured using the Beck Depression Inventory (BDI-II) [46].

### Randomisation and blinding

Randomisation will be carried out after consent is gained for participation in the main trial for those participants who are eligible. A remote randomisation procedure will be used through an online system based at the King’s Clinical Trials Unit at the Institute of Psychiatry, King’s College London. This involves allocation of unique identification numbers for each participant. The minimisation method will be used for the allocation that involves stratification by severity of alcohol dependence (SADQ score of over 40 or under 40), site and age (18 to 29, 30 to 39, 40 to 49 or 50 to 60). These variables are known to be potential confounders with the observed outcome and are collected at preliminary screening.

As this is a multi-centre study and allocation is blind, those conducting the randomisation will not be in a position to subvert the allocation sequence. The blister packs contain 7 tablets and will be supplied in individual cartons with a label on the front face of the carton bearing a unique kit identification number (Kit ID). The Kit ID is pre-printed on the label by the packaging company. Participants will be allocated Kit IDs according to the remote randomisation procedure. Each carton sent to the Pharmacy by the manufacturing company will be accompanied by an individual sealed code-break envelope in case of emergency unblinding. Participants, researchers and ward staff will be blind to which treatment each patient is given.

### Pharmacological treatment

The duration of treatment with mifepristone/placebo is 2 weeks, while participants are an inpatients in the alcohol treatment units. The daily dose will be three 200 mg tablets a day (morning, afternoon and evening) for 7 days followed by two 200 mg tablets a day (morning and evening). These doses are based on previous studies of the effectiveness and toxicity of mifepristone.

The participants will receive normal clinical care while on the unit, and concurrent medical and psychiatric disorders will be treated as required. This includes prescription of a benzodiazepine (normally chlordiazepoxide) to protect against the tremor and convulsive aspects of acute alcohol withdrawal. Benzodiazepine treatment is normally given to patients during the first 7 to 10 days of detoxification, as required, and this treatment will not be altered during the trial. All prescriptions of any drug treatment given to trial participants will be recorded during the trial.

All participants will receive the standard care provided by the participating alcohol treatment services. This includes access to all the facilities provided by the services, including psychotherapy, pharmacotherapy, inpatient and residential rehabilitation. These services are normally provided for up to 3 months per episode of care. Participants who relapse or seek further treatment will be offered additional care, in keeping with standard clinical policies.

### Assessment of efficacy

Figure 1 presents an overview of the trial protocol.

**Fig. 1 Fig1:**
[figure not shown]
Trial procedure timeline

### Primary outcome measures

Cognitive ability will be measured using the CANTAB. The CANTAB has been used extensively in research and previous studies have been published that have used the CANTAB test battery in patients with depression and patients with alcohol dependence [47–52]. The CANTAB testing will compare mifepristone and placebo groups concurrently. Cognitive function measurement prior to mifepristone/placebo would not be valid owing to intoxication. A pretest will be carried out on the day before the first CANTAB testing, composed of the Motor Screening task and the Reaction time task. These two tests are designed to assess basic motor and visual skills and determine whether participants are capable of being tested on CANTAB. The CANTAB tests that will be used at the two cognition testing times (between days 13 and 20 and 21 and 28) are: visuospatial ability by Reaction Time, Pattern Recognition, Matching to Sample Visual Search, Spatial Recognition memory and Paired Associates tasks; sustained attention by the Rapid Visual Processing task; and executive function by Intra- and Extra-Dimensional Shifting, Spatial Working Memory and Stockings of Cambridge tasks.

The above CANTAB test times will enable examination of cognitive testing administration of chlordiazepoxide ceases, as benzodiazepines are well established to affect memory and learning. Urine samples taken on the day of CANTAB testing will be screened for the presence of residual chlordiazepoxide or its active metabolites, which may affect cognitive performance [53].

The BDI-II [46] will be used to record symptoms of depression throughout the trial. It will be administered at every 7 days during the 4 weeks the participant is in the trial and at 3, 6 and 12 months follow-up from cessation of drinking. The BDI-II will be administered on the day of the CANTAB testing so that the results can be used as a variable in the measure of cognitive function.

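### The main CANTAB comparison names no covariate, and the post hoc list takes in post-randomisation variables but omits the screening MMSE; the cost is some precision, not validity

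*Protocol article*

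**What the plan says.** All references are to the protocol article.

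- **Objectives:** the first objective is "To compare effects of mifepristone and placebo in preventing memory loss and depressive symptomatology in alcohol-dependent persons undergoing alcohol detoxification".
- **Primary outcome measures:** CANTAB is given twice, on days 13 to 20 and days 21 to 28. There is no earlier test because "Cognitive function measurement prior to mifepristone/placebo would not be valid owing to intoxication". The contrast is between arms: "The CANTAB testing will compare mifepristone and placebo groups concurrently".
- **Study entry:** the screening appointment before admission "included administration of the Mini-Mental Sate Examination (MMSE) [39] to screen for any severe cognitive impairment".
- **Randomisation and blinding:** minimisation uses "stratification by severity of alcohol dependence (SADQ score of over 40 or under 40), site and age". No cognitive score is among the factors.
- **Statistical analysis:** the main analysis of CANTAB is an ANOVA of the two arms, and no covariate is named for it.
- **Post hoc analysis:** an ANCOVA will examine withdrawal severity (CIWA-Ar and AUQ), depressive symptoms, smoking, chlordiazepoxide dose, medication prescribed after detoxification, psychiatric comorbidity, other medication and age. The MMSE is not listed.

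**The concern.** A covariate in a randomised comparison should be measured before randomisation and should predict the outcome. It does not have to be a clean measurement: noise from intoxication weakens the gain but introduces no bias. The screening MMSE meets the timing condition and is already collected, but the article gives it no role after entry. Several covariates that are listed fail the timing condition. The drug could affect them, so adjusting for them could remove part of its effect.

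The Background reports cognitive deficits in 50 to 80% of dependent patients, so prior cognition probably varies widely between participants. If the MMSE captures even some of that variation, leaving it out of the main model gives up power that would cost almost nothing to recover.

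**Working it through.** **1. Timing of the covariates**

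The Abstract places randomisation at admission.

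| Variable | When it arises, according to the article | In the post hoc list? |
|---|---|---|
| CIWA-Ar | daily from 24 h after the last drink | yes |
| Chlordiazepoxide dose | usually the first 7 to 10 days of detoxification | yes |
| Medication after detoxification | after detoxification | yes |
| Depressive symptoms | time not fixed in the list; Primary outcome measures plans to use the BDI-II from the CANTAB day | yes |
| AUQ | at screening and weekly from 24 h; the list does not say which | yes |
| Age | before randomisation | yes |
| MMSE | at screening, before randomisation | no |

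**2. The article's own sample size**

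Inputs from Sample size: effect 0.5 SD, power 80%, alpha 0.05 (two-sided assumed).

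n per arm = 2(1.960 + 0.842)² / 0.5² = 62.8, so 63. The stated 63 reproduces. The article plans 120 in total, so 60 per arm is used below.

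**3. Power without adjustment, 60 per arm**

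SE = √(2/60) = 0.1826 SD. 0.5/0.1826 = 2.739, and 2.739 − 1.960 = 0.779, so power is 78.2%.

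**4. Power with one baseline covariate**

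The residual SD is √(1 − r²), where r is the correlation of the MMSE with the CANTAB score. The article gives no r, so a range is shown.

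| r (assumed) | Variance removed | Residual SD | Power, 60 per arm | n per arm for 80% |
|---|---|---|---|---|
| 0 | 0% | 1.000 | 78.2% | 63 |
| 0.2 | 4% | 0.980 | 79.8% | 61 |
| 0.3 | 9% | 0.954 | 81.9% | 58 |
| 0.5 | 25% | 0.866 | 88.5% | 48 |

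Estimating the covariate slope inflates the variance by about 1 + 1/(120 − 4), under 1%, which the table ignores.

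**5. The 27 recruited**

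Trial status gives 26 + 1 = 27, taken as 13 v 14. With one roughly normal covariate, the expected variance relative to no adjustment is about (1 − r²)(1 + 1/(27 − 4)) = (1 − r²) × 1.043.

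- r = 0.2: 0.96 × 1.043 = 1.00, no gain
- r = 0.3: 0.91 × 1.043 = 0.95, a 5% gain
- r = 0.5: 0.75 × 1.043 = 0.78, a 22% gain

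Break-even is at r² = 1/24, or r = 0.20.

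**6. How far a chance imbalance could move the result**

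Only r times the imbalance in the baseline score reaches the CANTAB contrast.

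- 60 per arm: the SE of the imbalance is 0.183 SD, with a 95% range of ±0.36 SD. The shift is at most about ±0.07 SD at r = 0.2, ±0.11 at 0.3 and ±0.18 at 0.5.
- 13 v 14: SE = √(1/13 + 1/14) = 0.385 SD, with a 95% range of ±0.755 SD. The shift is at most about ±0.15, ±0.23 and ±0.38 SD.

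This variation is already part of the unadjusted standard error.

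**The case against.** The strongest reply is that nothing here is biased. Allocation is randomised and concurrent, chance imbalance sits inside the standard error and the 5% type I error, and minimisation already balances dependence severity, site and age. All of that stands, and it limits the point to precision.

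A reader might infer more in three places, and the article does not support it.

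- **That the protocol contradicts itself** by using an MMSE while calling pre-treatment measurement invalid. The MMSE is used only "to screen for any severe cognitive impairment". That is compatible with judging intoxicated patients unfit for detailed outcome testing.
- **That a difference at weeks 3 to 4 could simply be a pre-existing one**, because with 27 patients a baseline imbalance above 0.4 SD has a 30% chance and the design effect is 0.5. The two figures are on different scales. At r = 0.3 an imbalance of 0.4 SD moves the outcome by 0.3 × 0.4 = 0.12 SD.
- **That prevention of memory loss cannot be studied without a baseline.** Less deficit than on randomised placebo is a legitimate comparative meaning, and both the hypotheses and the stated null are between-arm comparisons.

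It can also be said that a full covariate model may stand in an analysis plan not shown here. That is possible. However, the article itself names the main analysis and sets out a covariate list, and the point concerns what those two statements contain.

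Finally, the MMSE may predict CANTAB poorly. Scores may bunch near the maximum, intoxication adds noise, and excluding severe impairment narrows the range. This is fair, and it is why the low end of the table should be expected.

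**Conclusion.** The point holds as a modest matter of efficiency and covariate choice. The article's only described pre-randomisation cognitive score is left out of the analysis of a cognitive primary outcome, while variables that treatment could alter are listed.

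At the planned 60 per arm, the gain is about 1.6 percentage points of power at r = 0.2 (79.8 − 78.2) and 3.7 at r = 0.3 (81.9 − 78.2). It reaches 10.3 points only at r = 0.5 (88.5 − 78.2). At the 27 recruited it is about nil at r = 0.2, 5% of the variance at r = 0.3, and useful only above that. Every figure rests on an assumed correlation.

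The validity of the randomised comparison is not in question. The design does not measure within-person change in cognition, so that is the one claim the results cannot carry. The Background also links deficits to the number of earlier withdrawal episodes ("the severity of cognitive deficits in alcohol-dependent persons was correlated not only with a greater number of withdrawal episodes"). The article does not show whether that history was recorded, so nothing further is concluded from it.

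**What to change.** 1. Before the data lock described under Data management, pre-specify the screening MMSE total as a covariate in the main CANTAB model. Keep the unadjusted comparison as a sensitivity analysis.
2. Tabulate the MMSE by arm with the other baseline characteristics.
3. Keep covariates that arise after randomisation out of the main model. If the post hoc ANCOVA uses them, say that treatment may affect them and that the adjusted contrast is exploratory.
4. Report the finding as a between-arm difference in cognitive performance at weeks 3 to 4, not as within-person loss prevented.

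The cost is one degree of freedom and a sentence in the analysis section. No new data are needed, so the change remains possible although recruitment has closed. With 27 participants and r near 0.2 it neither helps nor harms materially.

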### Assessment of safety

The procedures involved in this research are unlikely to cause significant discomfort or distress to participants. All questionnaire measures and research procedures have been widely validated and used in previous research without causing any problems to participants. Mifepristone has a good safety record and has been used clinically for over 15 years for other applications. However should any distress or discomfort occur with any of the procedures trained medical and nursing staff will be available on a 24 h basis to provide help and support. All staff involved in the care of trial participants will receive training on the conduct of the trial protocol. In particular training will be provided on the detection and management of expected and unexpected adverse drug events.

The collection and reporting of Adverse Events will start following the first dose of the trial medication and will continue until the last dose of the trial medication. Reporting of Serious Adverse Events, Serious Adverse Reactions and Suspected Unexpected Serious Adverse Reactions will continue until 14 days after stopping the trial medication. All concomitant medications will be recorded until 14 days after stopping the trial medication.

Daily assessments by the clinical team to monitor for signs of nausea or fatigue that might indicate adrenal insufficiency will be made. Analysis of the plasma samples that will be taken on days 1, 7 and 14 of the mifepristone/placebo administration will ensure that the electrolyte levels remain within normal limits (sodium 135–145, potassium 3.5–5.3, chloride 95–105, urea 3.3–6.7, creatinine 40–120, all units micromoles per litre). Blood pressure checks were carried out daily during the acute withdrawal phase (10–14 days) as part of the normal clinical routine, and on day 14 if not measured on that day as part of normal clinical care. In the event of a participant self-discharging from the unit before the course of mifepristone is completed, the mifepristone/placebo treatment will be stopped and the participant will be withdrawn from the trial.

Following recruitment of the first 20 participants the Data Monitoring Committee will carry out a detailed examination of the safely data to ensure that there no problems have arisen with regard to drug safety.

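### The first CANTAB window opens on day 13, inside the 14-day dosing period and before the stated week 3, so first sessions can mix a current drug effect with lasting protection

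*Protocol article*

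**What the plan says.** The passages that bear on timing, all in the protocol article:

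- **Abstract, Methods/Design:** "Primary outcome measures are cognitive function at week 3 and 4 after cessation of drinking". Treatment starts at admission: "On admission participants are randomised to receive 600 mg a day of mifepristone".
- **Methods/Design (main text):** after describing two weeks of treatment, "They will then remain in the trial for a further 2 weeks undergoing cognitive testing and questionnaires".
- **Pharmacological treatment:** "The duration of treatment with mifepristone/placebo is 2 weeks, while participants are an inpatients in the alcohol treatment units".
- **Assessment of safety:** dosing days are numbered up to 14, with "plasma samples that will be taken on days 1, 7 and 14 of the mifepristone/placebo administration".
- **Primary outcome measures:** "two cognition testing times (between days 13 and 20 and 21 and 28"). Also, "A pretest will be carried out on the day before the first CANTAB testing", so the pretest can fall on day 12.

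The Aims section asks whether treatment in acute withdrawal protects against memory loss afterwards, during abstinence. The only reason given for the CANTAB timing is that chlordiazepoxide should have stopped, and the urine screen on test days looks for that drug and its metabolites only. The text does not say from which event the CANTAB days are counted. The timeline figure might, but it could not be seen.

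**The concern.** Two descriptions of the primary cognitive assessment do not agree. One puts it in weeks 3 and 4, after treatment has ended. The other allows the first session while study drug is still being taken.

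This matters because the aim is a lasting effect. If mifepristone changes test performance only while it is present, a participant tested on day 13 shows that change even if nothing persists. A first-session difference could then be read partly as protection when it reflects current exposure.

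Nothing in the article separates the two:

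- There is no CANTAB before treatment, because of intoxication, so there is no within-person reference.
- The Cognitive performance section rules out a repeated measures analysis of cognition.
- The covariates listed under Post hoc analysis do not include whether study drug was being taken at testing.

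**Working it through.** **Reference figure.** The plan gives no figure for the timing question. The effect it is sized for, 0.5 SD, serves as a yardstick, and its sample size reproduces: n per group = 2 × (1.960 + 0.842)² / 0.5² = 62.8, rounded up to 63, as the Sample size section states. The timing point does not depend on this.

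**Step 1: overlap of window 1 with dosing.** Inputs are window 1 = days 13-20 (8 days), window 2 = days 21-28, and 14 consecutive dosing days starting no earlier than admission. Since the day origin is not stated, several conventions were tried.

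| Day numbering | Dosing days | Window-1 days on drug | Share of 8 days | Window-1 days before week 3 |
|---|---|---|---|---|
| Day 0 = cessation = first dose | 0-13 | 13 | 12.5% | 13 |
| Day 1 = cessation = first dose | 1-14 | 13, 14 | 25% | 13, 14 |
| Day 0 = cessation, first dose day 1 | 1-14 | 13, 14 | 25% | 13 |
| Day 1 = cessation, first dose day 2 | 2-15 | 13-15 | 37.5% | 13, 14 |
| Day 1 = cessation, first dose day 3 | 3-16 | 13-16 | 50% | 13, 14 |

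Week 3 is days 15-21 when counting from day 1 and days 14-20 when counting from day 0. Day 13 is on drug and before week 3 in every row. Window 2 contains no dosing day in any row.

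**Step 2: what the overlap could do to the first-session contrast.** Let f be the share of first sessions in the mifepristone arm taken on drug, and d the acute on-drug effect in SD units. If there is no lasting effect, the expected first-session difference is f × d. The documents give neither f nor d. For illustration, d is assumed to be 0.5.

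- f = 12.5%: 0.125 × 0.5 = 0.0625 SD
- f = 25%: 0.25 × 0.5 = 0.125 SD
- f = 50%: 0.50 × 0.5 = 0.25 SD

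The values of f are the shares of window days in the table. They equal the shares of sessions only if sessions are spread evenly over the window.

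**Step 3: chance of a significant favourable result at the planned size.** With 60 per arm and a two-sided 5% test, the probability is about Φ(f × d × √(60/2) − 1.96), ignoring the small extra variance from mixing sessions.

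- 0.0625 SD: Φ(0.34 − 1.96) = 5%
- 0.125 SD: Φ(0.68 − 1.96) = 10%
- 0.25 SD: Φ(1.37 − 1.96) = 28%

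With no effect of any kind the figure is 2.5%. Trial status reports 26 + 1 = 27 recruits. The probabilities are lower at that size, but the expected shift in SD units does not depend on sample size.

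**The case against.** The strongest reply is that this is a small inconsistency with little consequence. Only first sessions on the earliest days of the window are affected, nobody can say how many there were, and the second session is off drug and also primary. The analysis may classify sessions by timing in a statistical analysis plan that is not shown. Excluding sessions by a variable that arises after randomisation would also sit badly with the intention-to-treat analysis the article promises. Most of this stands. It limits the size of the problem and rules out simply deleting on-drug sessions. It does not remove the contradiction, which lies in the stated text and not in detail left to another document.

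A reader might infer four stronger things that the documents do not support:

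- **That days 13-14 were the likely choice, just before discharge.** The Abstract gives two weeks as a minimum inpatient stay, and the inpatient-only saliva collection is scheduled around day 20, so longer stays were expected.
- **That benzodiazepine carry-over adds to the problem.** The article already deals with it, through the urine screen on test days and chlordiazepoxide dosage as a covariate.
- **That the cited bipolar depression studies show an acute effect on cognition.** The Background reports a benefit on spatial working memory, a task also in this battery, but does not say whether patients were tested on drug. It makes a cognitive effect plausible, not specifically an on-drug one.
- **That a positive cognitive result could not answer the trial's question.** A current drug effect alone would not explain a difference on days 21-28.

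One further caution stands. The documents give no elimination time, so a session one day after the last dose is off treatment but not shown to be free of drug.

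**Conclusion.** The point holds as a reconcilable conflict with a bounded consequence. Under every ordinary numbering tried, at least one day of the first CANTAB window, and up to four of its eight days, falls within dosing. Day 13 always precedes the week named as primary. First-session results can therefore combine a current drug effect with the lasting protection the trial is meant to test.

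The size cannot be fixed from the documents. The range of about 0.06 to 0.25 SD rests on an assumed acute effect of 0.5 SD, no lasting effect, and 12.5% to 50% of first sessions on drug. The top of that range is half the effect the trial is sized for. It is an upper illustration, not an estimate. If no first session took place during dosing, the effect is nil. The change is worth making because it is cheap and bears directly on what the first session can show.

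**What to change.** **Protocol text.** Reconcile Primary outcome measures with the Abstract, Methods/Design and Pharmacological treatment. State the event from which CANTAB days are counted, and open the first assessment window after the last dose. This moves an assessment and leaves treatment as it is.

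**Data already collected.** Trial status says recruitment ended in May 2015, so the window can no longer be moved for these participants. Before unblinding:

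1. Derive days since last dose of mifepristone/placebo for each CANTAB session, in the same way in both arms, and report the distribution by session.
2. Keep all sessions in the intention-to-treat analysis.
3. Pre-specify an analysis of the first session restricted to sessions after the last dose.
4. Base any claim of lasting protection on off-drug sessions, meaning that restricted analysis and the days 21-28 session.

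**Cost.** One derived variable and one additional analysis. The restricted analysis has fewer first sessions and less precision, which is felt with 27 recruits. It also selects on a post-randomisation variable, so it should be reported beside the intention-to-treat result and not in place of it.
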